### Monitoring

#### Safety and adverse effects

WBV may cause some potential side effects, including headache, dizziness, itch, erythema, and fatigue. However, these symptoms normally disappear soon after removing the vibration stimulus. Participants will be sent to a medical institution if their symptoms exacerbate. Before the commencement of assessment and treatment, researchers in the current study will complete the experimental checklist including examination of the physical and mental conditions of participants, the intervention equipment, and the operational circumstances, so as to guarantee the safety of the experimental process. In addition, adverse events in the whole process will be traced. Staff working in the ethical committee will check the recorded documentation to ensure that intervention and assessment will not produce physical or mental damage to participants.

#### Auditing

Demographic information (e.g., name, gender, etc.) will be collected in this research program. fNIRS data will be gathered in the electronic format. Data in paper format include signed informed consent, self-reported functions, and adverse events. The above data will be organized and stored in an encrypted computer. The data monitoring committee is made up of a staff working in the department of laboratory management and a senior professor who studies in the area of rehabilitation and physical education. These individuals are independent of researchers in the present study and any other potentially competing interests, and they will check the integrity of data in the trial process.

To improve compliance, participants will be told about the benefits of rehabilitative programs. Additionally, material rewards (e.g., gifts and cash) will be offered during the experimental process. One of the authors will document the information relating to the participation in intervention involving attendance, details of the training program, and participant feedback. Participants will be encouraged to report any difficulties and these will be recorded by the training supervisor. All data collected in the process of intervention will be transferred into an electronic version and stored on an encrypted computer managed by a professional staff member in the laboratory. In addition, these data will be checked once a week by the researcher manager.

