Neuromuscular training, which usually refers to either proprioceptive drill, strength training, or a combination of both [23, 24], is an effective intervention modality in treating the sensorimotor deficits of individuals with CAI [25, 26]. However, it has not been fully determined as to which neurophysiological mechanism contributes the most to the benefits of neuromuscular training. Based on the existing hypothesis, the mechanism underlying the effect of neuromuscular training on sensorimotor deficits may be related to both spinal (e.g., altered H-reflex) and supraspinal adaptation (e.g., feed-forward reflexive mechanism) [4, 27, 28], yet relevant evidence is lacking for these hypotheses. As one form of neuromuscular training, whole-body vibration (WBV) has been widely studied in different areas such as sports [29], rehabilitation [30], and public health [31]. The possible mechanism of WBV benefits is that it could facilitate reflexive activation at both the spinal and supraspinal level in the central nervous system [32, 33]. To be specific, WBV has been shown to be capable of modulating spinal excitability in a human trial [34], and modulating synaptic plasticity [35, 36] and neurogenesis [37] in the brain of animals. Regarding the effectiveness of WBV for CAI, it has been found that additional benefits could be achieved in sensorimotor deficits (e.g., postural control, strength, and muscle activity) when WBV was added as a supplementary tool [38–40]. Nevertheless, it was still unknown whether the improvements in sensorimotor functions were associated with plastic changes in the brain for people with CAI. Investigation of the relationship between effectiveness of WBV and brain plasticity may provide understanding regarding the pathways through which WBV works on CAI [16].

Therefore, a single-blind randomized controlled trial will be designed to answer the following questions: (a) if WBV can generate sensorimotor benefits for patients with CAI? (b) is there a correlation between changes of sensorimotor functions and alterations of brain plasticity for participants with CAI? In this study, We hypothesize that there will be plastic changes in the brain after the WBV intervention, and these alterations will be correlated with changes in sensorimotor functions.

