### Randomization, allocation, and blinding

Concealed random allocation will be conducted by an independent researcher after the baseline testing using a sealed envelope filled with random numbers (1–99) generated by the software of Microsoft Excel.

Eligible participants will be allocated into 4 groups (Fig. 1):balance training (BT): undertaking balance training on the flat floor.whole-body vibration (WBV): standing on the vibration platform using one-legged stance and conduct the same tasks as BT group.whole-body vibration and balance training (WBVBT): performing balance training on the vibration platform.control group: no intervention.

Participants in all groups will be allowed to maintain their normal physical activity but avoid any therapeutic exercises of the ankle joint. As WBV stimulation can be easily felt, it is difficult to blind patients. Accordingly, blinding will only be performed on assessors.

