### Outcome measures

Sociodemographic information including name, sex, age, dominant leg, physical activity and level of kinesiophobia will be collected through online questionnaires. Self-reported measures consist of the CAIT and FAAM. Objective measures in the current study include sensorimotor function and brain plasticity. The primary outcome measures will be balance with SEBT end-point to determine sensorimotor deficit, and activation of brain area with oxyhemoglobin in determining brain plasticity. All measures of outcome will be performed by a qualified blinded assessor, who is independent of the current study, at the fitness laboratory of Zhejiang University. An adequate rest period, assessed with a rating of perceived exertion (Borg scale, 6–20), will be given between each of the two objective measures to avoid potential fatigue. Since TMS is potentially associated with alterations of functional performance, the test orders (Table 2) will be arranged to mitigate any mutual influence between each two tests. To avoid the influence of myopia on balance control, participants will be asked to wear any corrective eyewear throughout the test process. The extremity with the lower CAIT score will be tested if bilateral ankle instability exists. Outcome measures will be assessed before and after the WBV intervention. According to a previous study, there were delayed improvements in balance and self-reported functions for patients with CAIafter accepting balance training programs [56]. Hence, the follow-up assessments will be performed 2-week after the intervention program.

**Table 2 Tab2:** SPIRIT timetable including schedule of enrolment, interventions and assessments

	Study period					
	Enrolment	Baseline assessment	Allocation	Post-allocation	Post-intervention assessment	Follow-up
Time points	-4 to -1 weeks		0	1–6 Weeks	6–7 weeks	8–9 Weeks
Enrollment						
Eligibility screen	X					
Informed consent	X					
Random allocation			X			
Intervention						
WBV						
Assessment						
Primary outcome measures						
Brain activity						
Corticomotor Plasticity (TMS)		X			X	X
Activation of brain area (fNIRS)		X			X	X
Sensorimotor deficits						
Balance (SEBT&TIBT)		X			X	X
Strength (HHD)		X			X	X
Proprioception (AMEDA)		X			X	X
Functional performance (SHT)		X			X	X
Secondary outcome measures						
Ankle instability (CAIT)		X			X	X
Ankle function (FAAM)		X			X	X

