### Sensorimotor deficits

Static balance will be estimated through the Time-In-Balance Test (TIBT). In the TIBT, participants will stand on a firm surface in a single-legged stance. Participants will be instructed to put their hands on their spina iliaca. The time taken to keep balance with eyes closed will be recorded and referenced with a cutoff score of 25.89 s [57]. The maximum duration of the test is 60-s [58]. The test will be carried out with 1 practice trial and 2 measured trials with a 60-s interval between each test. The longest time between the two tests will be recorded as the final score. The outcome will be discarded and replaced by a new test if: (1) participants move the tested foot; (2) the contralateral foot touches the floor.

Dynamic balance will be assessed using the Star Excursion Balance Test (SEBT), which is an effective means for determining reach deficits of CAI individuals [59]. There will be 8-direction including anterior, anteromedial, medial, posteromedial, posterior, posterolateral, lateral and anterolateral in the SEBT test. During the test, participants will be asked to stand at the center point using the involved limb and put their hands on their spina iliaca. Then, participants will be asked to use non-stance limb to reach in each direction as long as possible. In each direction, the farthest point of the great toe will be marked and recorded. The score will be discarded under the following conditions: (1) participants shift or lift the involved limb; (2) balance can not be maintained during the test. Before the official test, participants will have 2 practice trials to familiarize them with the test procedure and setting. To calculate the final SEBT score, the length of the lower limb measured from the anterior–superior iliac spine to the medial malleolus at the supine position will be used to divide the reach distance using the method described previously [60]. Besides, changes in SEBT scores will be examined to see if they reach the minimal detectable change in eight directions, including 6.73% (medial), 8.56 (anterior), 8.68 (anteromedial), 9.69 (anterolateral), 12.17 (lateral), 13.00 (posterior), 13.33 (posterolateral) and 13.36% (posteromedial) [61].

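### Telling unblinded participants about programme benefits to raise compliance can add avoidable expectation bias to training-versus-control comparisons, including on the primary SEBT

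*Protocol article*

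**What the plan says.** The second paragraph of the protocol article's Auditing section deals with adherence: "To improve compliance, participants will be told about the benefits of rehabilitative programs". It adds material rewards and records of attendance. It does not say which arms hear the message, when, or in what words.

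Four other places bear on it:

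- **Background**, question (a): "if WBV can generate sensorimotor benefits for patients with CAI".
- **Randomization, allocation, and blinding**: "As WBV stimulation can be easily felt, it is difficult to blind patients", and hence "blinding will only be performed on assessors". The fourth arm is defined as "control group: no intervention".
- **Outcome measures**: "The primary outcome measures will be balance with SEBT end-point to determine sensorimotor deficit, and activation of brain area with oxyhemoglobin in determining brain plasticity".
- **Sensorimotor deficits**, on the SEBT: "participants will be asked to use non-stance limb to reach in each direction as long as possible". The same section times the side-hop test at maximal speed and measures voluntary isometric strength. CAIT and FAAM are completed by the participants themselves (Self-reported outcomes).

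The limitations paragraph in the Discussion mentions neither the lack of participant blinding nor expectation.

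**The concern.** A blinded assessor protects how a score is read and recorded. He or she cannot protect how hard the participant tries. In the SEBT the participant decides how far to reach, within the limits of balance. A participant who has been told that the programme helps, and who knows that he or she received it, may try harder or rate the ankle more favourably than one who received nothing.

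Part of this cannot be avoided once vibration is felt and no sham is used, and the protocol says openly that patients are hard to blind. The compliance message is different. It is a planned step that the investigators can choose not to take, and it presents benefit as known in a trial that asks whether benefit exists. What is at stake is the reading of a training-versus-control difference on one of the two primary outcomes and on several others: some of it could reflect motivation, and the design cannot separate the two.

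**Working it through.** **1. The plan's own figure.** The Sample size section gives 64 in total before dropout and 80 after. With f = 0.35, m = 3 measurements, 4 groups, α = 0.05 and an assumed correlation of 0.5 between measurements (not stated in the article), the between-groups F test of a repeated-measures ANOVA has

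λ = N·f²·m / (1 + (m − 1)·ρ) = 64 × 0.1225 × 3 / 2 = 11.76, with df 3 and 60.

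Power is 0.805; N = 60 gives 0.774. So N = 64 reproduces, and 64 / (1 − 0.2) = 80, or 20 per group. The point raised here does not change these numbers. They only set the group size for the illustration.

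**2. Which outcomes are exposed.**

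| Outcome | Route for expectation |
|---|---|
| SEBT (primary) | voluntary maximal reach |
| Side-hop | maximal speed |
| Isometric strength | voluntary force |
| CAIT, FAAM | self-rating by unblinded participants |
| fNIRS oxyhemoglobin (primary) | recorded over a fixed 60 s stance; less direct |

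**3. Which comparisons are exposed.** BT, WBV and WBVBT all follow a supervised programme, and the message is worded generally. Control follows none. The exposure is therefore training versus control. Because the control arm is one of the four groups in the planned one-way and repeated-measures ANOVAs, the omnibus tests carry it too.

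**4. Illustration of size.** The document gives no expectation effect, so a shift b (in SD units) is assumed. Suppose there is no true effect and the message moves all three training arms by b against control. The group means are (b, b, b, 0), with grand mean 3b/4. Then

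f² = [3·(b/4)² + (3b/4)²] / 4 = 3b²/16.

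With 20 per group, N = 80 and λ = N·f² = 15b². The test is F with df 3 and 76 at α = 0.05, applied to a comparison made after the intervention.

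| b (assumed) | λ | Rejection rate |
|---|---|---|
| 0 | 0 | 5.0% |
| 0.05 | 0.0375 | 5.2% |
| 0.1 | 0.15 | 5.8% |
| 0.2 | 0.60 | 8.6% |
| 0.3 | 1.35 | 13.6% |
| 0.5 | 3.75 | 32% |

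With 16 per group (64 completers) the rates at b = 0.1 and 0.2 are 5.7% and 7.8%. The group-by-time interaction, with the shift present after baseline only and correlation 0.5, gives 5.8% and 8.3% at 20 per group.

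**5. Which rows apply.** The rows for 0.3 and 0.5 SD are better read as a possible total expectation gap between unblinded training and no intervention. Most of that gap would come from the design. Only the increment due to the message is at issue, so the working range is 0.05 to 0.2 SD, which is itself an assumption.

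**The case against.** The strongest reply is that the point rests on one sentence. The article gives no script, and the exact wording would normally sit in the full protocol or participant materials, which are not shown. Question (a) concerns WBV, whereas the message concerns rehabilitative programmes in general, and the Background already describes neuromuscular training as effective in CAI. Participants cannot be blinded and no sham is planned, so most expectation would exist without the sentence. Loss of balance voids an SEBT attempt, so effort alone does not set the score.

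Much of this stands, and it limits the size of the point. It does not remove it: the message is a stated procedure rather than an omission, and WBV is among the programmes it covers.

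A reader might infer more than the text supports:

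- *That the message lowers expectation in the control arm.* The article does not say whether controls hear it.
- *That it biases comparisons among BT, WBV and WBVBT.* All three are supervised programmes under a general message, and nothing suggests a difference between them.
- *That it is the only avoidable source of expectation, or that rewards differ by arm.* Neither is stated.
- *That false-positive rates reach 34% or 48%.* Those follow from a 0.5 SD shift with an unadjusted two-arm t test, or with the three training arms pooled against control. The plan has ANOVA followed by Bonferroni-adjusted post-hoc tests and contains no pooled contrast, and 0.5 SD would attribute to one sentence what the whole design may produce.

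**Conclusion.** The point holds as a minor, avoidable weakness. A planned benefit message, given to participants who know their arm in a trial with a no-intervention control, can add expectation bias to training-versus-control comparisons on the SEBT, side-hop, strength, CAIT and FAAM. It bears less on fNIRS. Its size is unknown. Under the assumed increment of 0.05 to 0.2 SD, shared equally by the three training arms and with no true effect, the error rate of the planned one-way ANOVA moves by between 0.2 and 3.6 percentage points above the nominal level. No stated figure is wrong, no passages contradict each other, and the sample size is unaffected. Removing the sentence would reduce expectation bias but not eliminate it, because the unblinded design without a sham remains.

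**What to change.** Replace the sentence in the Auditing section with neutral information, scripted and given identically to all four arms. It should say that the trial is testing whether, and by how much, the programmes differ, and that attendance and full effort at every assessment matter equally in every group. For compliance, rely on what is already planned: therapist supervision, attendance records and rewards.

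The cost is wording in the protocol and in the participant script. No extra participants, visits or analyses are needed. The downside is possibly slightly lower motivation to attend training, which the existing supervision and rewards should partly offset.

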#### Ethics and dissemination

The present study has been approved by the Medical Ethics Committee of the Department of Psychology and Behavioral Science of Zhejiang University (NO. 2,022,095). This ethical committee will be responsible for guaranteeing the rights, safety, and medical care of participants throughout the experiment. Further, the current study was registered in the Chinese Clinical Trial Registry (NO. ChiCTR2300068972) on 02 March 2023. The results of the current study will also be submitted to peer-reviewed journals and reported at conferences.

## Discussion

To the best of our knowledge, this will be a first study to assess the effect of WBV on brain plasticity in people with CAI. In addition, it will also investigate whether plastic changes in the brain correlate with the observed sensorimotor alterations. As consideration of plastic changes in the brain has become increasingly essential for understanding the mechanism of CAI, the current trial may provide evidence for the use of WBV in resolving sensorimotor deficits in patients with CAI.

Presumably because of the safety, efficacy, and efficiency, WBV has been the focus of increasing attention with respect to populations with frailty [75] and medical conditions [76, 77]. Our previous work, conducted by systematically reviewing the existing studies investigating WBV in CAI deficits, found that adding WBV to balance training could yield additional benefits in balance, strength, proprioception, and muscle activities of individuals with CAI [40]. Researchers involved in the previous studies speculated that the effect of WBV on the spinal reflex may be considered as one of the mechanisms, whereas the impact of WBV on the brain has been neglected to some extent [38, 53]. Since plastic changes in the brain were found to be closely associated with functional changes for individuals with CAI [14, 78], it is necessary to explore the role of brain plasticity in functional changes after intervention programs. On the other hand, it has been shown that plastic changes in the brain could be altered by the specific intervention forms, while the evidence related to WBV is lacking. For instance, 6-week stroboscopic balance training can change brain activities for athletes with CAI [21]. Similarly, transcutaneous electrical nerve stimulation and transcranial direct current stimulation were able to improve neural excitability [22, 79]. WBV has been demonstrated to be capable of modulating synaptic plasticity in animals [35, 36] and cortical activation among healthy people [33, 51], yet none of the studies have been done to examine whether WBV can induce neuroplastic changes in patients with CAI. Hence, it seems of value to investigate whether WBV can lead to benefits in sensorimotor function based on alterations occurring in the brain.

The stimulation of the motor cortex by TMS is a way to investigate the integrity of the brain in regards to muscle pathways and the functionality of cortical networks [80]. The changes from TMS (e.g., RMT, AMT, and CSP) observed in previous studies have indicated that there may be limitations in signal transmission from corticomotor systems to muscles around the ankle [12, 69, 81]. These alterations can be used to explain the changes in biomechanics [82] and kinematics [83] for individuals with CAI. In the current study, results of TMS assessments will be used to determine if there are associations between the sensorimotor changes caused by WBV intervention and alterations in the corticospinal pathway. fNIRS can be viewed as a non-invasive approach to assess functional activation of the brain through cerebral oxygenation changes evoked by haemodynamics [71]. A previous study using fNIRS to investigate alterations of cortical activation found significant differences in cortical-activation variability among individuals with CAI in comparison to a healthy control group [13], indicating that patients with CAI may have different patterns of cortical activation. In the present research, the changes in functional activations when participants stand in a one-legged stance can show how the cortical sensorimotor region responds to the instability of the ankle joints. In addition, the correlation between brain activation and alteration in sensorimotor function may provide evidence to support the strategy of taking brain activation as the target to achieve functional benefits.

Some limitations should be mentioned for the present study. First, compared to participants recruited at a university, patients from the community may have lower compliance because of their holiday, employment or family routines. Second, although participants will be requested to refrain from involvement in specific rehabilitation programs during the experiment, they will not be limited in regard to participation in regular exercises, which may be a factor influencing final outcomes. Third, despite the break provided between each of the tests, the results for brain plasticity and sensorimotor deficits may be interactively influenced, since these two measures are potentially associated [84]. Fourth, prognostic factors such as demographic features (e.g., age, sex), severity of lateral ankle sprain, anatomic configuration, functional performance, and initial treatment could potentially impact on the efficacy or mechanism of WBV, but this study may not be able to explain them clearly [85].

In conclusion, the main purpose of the current study is to explore the role of brain plasticity in the effects of WBV on sensorimotor deficits for individuals with CAI. The findings of this study will provide evidence for treating sensorimotor deficits from the perspective of brain plasticity. In addition, the results may also guide clinical practice when incorporating WBV into rehabilitation programs.

